### 2.3. Study Scope and Population

This single-center study will be carried out in an academic setting at the Faculty of Health Sciences of the University of the Atlántico Medio (Las Palmas de Gran Canaria, Spain) during the second semester of the 2025–2026 academic year. The target population will be second-year students of the bachelor’s degree in nursing enrolled in the course “Reproductive Health Nursing and Sex Education”.

The inclusion criteria are as follows: active enrollment, face-to-face attendance, and technological access. Students repeating the course, students with prior specialized training, and students with uncorrected sensory impairments will be excluded. The criteria for withdrawal once the study begins include incomplete data, abandonment of the session before the simulation is concluded, technological failure, or detected cross-contamination.

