-Satisfaction: The students’ subjective perception of the usefulness, fun, and motivation generated by the activity will be evaluated using the Gameful Experience Scale (GAMEX) [28]. This validated 27-item instrument in Spanish is suitable for measuring game experience in nursing students’ training. It uses Likert-type responses to measure the multidimensional nature of the gamified experience in the educational context. The six dimensions include enjoyment, abstraction, creative thinking, activation, absence of negative effects, and mastery. This model demonstrated high overall reliability, with a Cronbach’s alpha of 0.85. The scoring format uses a five-point Likert scale. In the proposed study, measurement will be conducted exclusively at the end of the intervention (Session 4) to capture the students’ overall perception of the program. Prior to analysis, items with negative wording (reverse punctuation) will be recoded so that higher scores consistently reflect a more positive experience. The statistical report will present results for both the total aggregate score and the independent mean scores for each of the six dimensions.-Player Profile: the students’ psychological and behavioral predisposition to game dynamics and narratives will be assessed using the PPDS in its validated Spanish version [21]. The PPDS is a psychometrically validated instrument composed of 21 items rated on a six-point Likert scale specifically designed to identify player profiles in the context of educational gamification based on narratives to measure the frequency of certain behaviors, where 1 means “Never” and 6 means “Always”. After a student completes the questionnaire, the system does not place them in a single category but generates five independent scores, one for each profile, showing which of the following profiles they align with the most: Tryhard (achievement- and competency-oriented); Coacher (oriented toward leadership and help); Esthetic (narrative and visual beauty-oriented); Joker (oriented to humor and surprise); or Toxic (a technical gamification term referring to players oriented toward testing system limits, seeking loopholes, or disrupting boundaries, often associated with lateral thinking rather than a negative personal judgment). The scale demonstrated high overall reliability (omega = 0.93).-Gamification Experience: Previous experience in gamification will be evaluated using the following question: Have you participated in similar activities before? The students can respond “yes” or “no”.-Sociodemographic variables: Age is understood as the time that a person has lived, counting from birth to the time of the survey, measured in whole years; gender is understood as a variable that refers to the social and cultural construction that defines the roles, behaviors, activities, and attributes that a society considers appropriate, with the answer options male, female, and non-binary; and the average grade considered to mean the average grade achieved in the first year of the nursing program to monitor the differences between the groups.-Feasibility and implementation outcomes: given the pilot nature of this trial, the following feasibility metrics will be formally tracked to inform the design of the subsequent definitive trial: recruitment rate, retention rate, technical failure rate, time-on-task compliance, and qualitative evidence of cross-contamination.

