As the researcher is also the teacher who evaluates the coursework, this could introduce unconscious bias (Pygmalion Effect) to favor the EG or generate in the students a desire to please the teacher by responding positively to the surveys. To address this situation, the knowledge-assessing questionnaires contain multiple-choice questions to facilitate automatic and objective correction and eliminate subjectivity on behalf of the evaluator. Anonymity will be guaranteed for the satisfaction surveys to encourage honesty.

As for the profile self-evaluation through the PPDS, the classification of the students depends on their sincerity when answering the test. It may be that a “Toxic” student does not recognize themselves as such and marks “Coacher” answers due to social desirability, thus being assigned a narrative that does not correspond accurately to their profile. This issue will be addressed by clearly explaining that there are no “good or bad” profiles, thus reducing social pressure.

Another limiting aspect is the risk of contamination between groups. As students are classmates from the same faculty, the CG students may learn about the existence of the EG’s “special missions” and feel demotivated (demoralizing effect) or try to obtain the EG passwords. To address this issue, Wix login passwords will be changed on a per-session and group basis, and explicit confidentiality will be required as part of the “game contract”. To actively monitor this risk without increasing survey fatigue, the Principal Investigator will utilize the pre-established “field diary” to record any spontaneous student disclosures or observable evidence of cross-contamination between the shifts. Any detected contamination will be reported as a feasibility metric and factored into the interpretation of the exploratory efficacy results. While this observational approach is suitable for a pilot, future definitive trials will benefit from incorporating a formal self-report question to empirically measure cross-contamination rates.

Finally, as a logistical limitation, and given the nature of the study, failures in the faculty’s Wi-Fi connection, Wix server crashes, or problems with students’ mobile devices could interrupt the intervention. An alternative plan will be available, with changes in the teaching schedule agreed upon with the students so that a new practical session may be scheduled.

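### Cross-contamination is captured only passively through the teacher-investigator's diary, so it is likely understated, and the fate of detected cases in the analysis is not settled

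*Protocol article*

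**What the plan says.** Section 2.8 names the feasibility metrics to be formally tracked for the later trial: "recruitment rate, retention rate, technical failure rate, time-on-task compliance, and qualitative evidence of cross-contamination". Section 3 describes feasibility as the primary outcome.

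Section 4.1 says how contamination is captured. The Principal Investigator keeps a field diary "to record any spontaneous student disclosures or observable evidence of cross-contamination between the shifts". Whatever is found is reported as a feasibility metric and taken into account when the efficacy results are read. The stated reason for not asking students is survey fatigue. The authors call the approach suitable for a pilot and add that "future definitive trials will benefit from incorporating a formal self-report question to empirically measure cross-contamination rates".

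Three other statements bear on how full the diary will be:

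- Section 4.1, on the investigator's dual role: "As the researcher is also the teacher who evaluates the coursework".
- Section 4.1, on the game contract: "explicit confidentiality will be required".
- Section 2.3, on withdrawal once the study has begun: "abandonment of the session before the simulation is concluded, technological failure, or detected cross-contamination".

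Section 2.10 states that the article is the full protocol and analysis plan and that no separate plan exists.

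**The concern.** The diary fills only if a student volunteers something to the teacher or the teacher notices it. A student who speaks up may be admitting a breach of the game contract to the person who evaluates the coursework, and the event is also a listed ground for withdrawal. Section 4.1 expects students to want to please this teacher when they answer surveys, but applies no such caution to the diary.

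Two things are at stake. First, an empty or thin diary could be read as evidence that separating the shifts and rotating the passwords worked (section 4), when it could not show that. The next trial's design and the reading of the learning-gain comparison both draw on it. Second, if detected cases are removed from the data, participants are lost after allocation because of an event that depends on detection and may differ by arm.

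**Working it through.** **No plan figure to reproduce.** The protocol gives no contamination rate, detection probability or threshold. What follows is a reading of the text and an illustration on assumed inputs.

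**Step 1: what each capture route can see.** The diary has two routes, disclosure and observation, and both run through the investigator. Observation is a real route: under section 2.7 the investigator monitors the sessions, is the only platform administrator and sees the form answers in real time. But the risk described in section 4.1 is classmates learning of the other arm's missions or seeking its passwords, and much of that would happen outside the sessions. The shifts are consecutive and the multiple-choice questions are identical in both arms (sections 2.5 and 2.7), so test content could also pass between them unseen. Barring false positives, passive capture can equal the true count or fall below it.

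**Step 2: how large the shortfall could be.** Let k be the number of students truly contaminated and s the chance that each is recorded by either route. Both are assumed. The cohort is 38 (18 + 20, section 2.7).

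- Expected number recorded = k × s
- Chance that none is recorded = (1 − s)^k, if students are detected independently

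| k (share of 38) | s = 0.1 | s = 0.3 | s = 0.5 | s = 0.8 |
|---|---|---|---|---|
| 2 (5.3%): expected recorded | 0.2 | 0.6 | 1.0 | 1.6 |
| 2: chance none recorded | 0.81 | 0.49 | 0.25 | 0.04 |
| 5 (13.2%): expected recorded | 0.5 | 1.5 | 2.5 | 4.0 |
| 5: chance none recorded | 0.59 | 0.17 | 0.03 | <0.001 |
| 10 (26.3%): expected recorded | 1.0 | 3.0 | 5.0 | 8.0 |
| 10: chance none recorded | 0.35 | 0.03 | 0.001 | <0.001 |

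For k = 5: 0.9^5 = 0.59, 0.7^5 = 0.17, 0.5^5 = 0.03. Independence is doubtful, because sharing a password involves at least two students. If cases were detected all together or not at all, the chance of an empty diary would rise to 1 − s. At s = 0.3 that is 0.70 instead of 0.17 for k = 5.

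**Step 3: what happens to a detected case.** Section 2.3 lists detection as a withdrawal criterion. Section 4.1 has it reported and weighed in interpretation. The missing-data rule in section 2.10 covers incomplete sessions only. None of the three says whether a detected student's scores stay in the global learning-gain comparison. Each student removed is 1/18 = 5.6% or 1/20 = 5.0% of an arm.

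**The case against.** The authors have met part of this already. They call the method observational, give a reason for it, and recommend a formal question for the definitive trial, so an empty pilot diary would not by itself leave the next trial without measurement. The outcome is labelled qualitative evidence, not a rate, and no go/no-go threshold depends on it.

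The deterrent is also inferred. The confidentiality clause is aimed at sharing between groups, and nothing says it bars telling the investigator. Nothing says students are told of the withdrawal criterion. Withdrawal costs a student little: everyone takes the sessions as normal teaching (section 2.6), and research data are analysed only after transcripts are locked (section 2.11).

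A student can, moreover, be withdrawn and the event still be reported, so sections 2.3 and 4.1 are not flatly incompatible.

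Most of this stands, and it limits how strongly the point can be put. It does not remove the two gaps. The authors acknowledge the missing question, but not that disclosure goes to the teacher under a contract and a withdrawal criterion. And the analysis status of detected cases is stated nowhere, in a document that says it is the whole analysis plan.

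**Conclusion.** The point holds in a limited form. Capture is passive and runs through the teacher-investigator, so understatement is the likely direction of error and an empty diary would not show absence of contamination. The amount cannot be derived from the document. For 5 contaminated students the chance of an empty diary runs from 0.59 to 0.03 as assumed detection goes from 10% to 50%, so no single figure should be quoted.

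A reader might infer that contamination is recorded only when a student volunteers it, and that the metric is bound to read too low. The text does not support that: observed evidence also counts, the outcome is qualitative, and the disincentive is plausible but not shown.

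The second part needs no assumed rate. Sections 2.3 and 4.1 leave the data of detected cases undecided, and one available reading removes participants after allocation, selectively on detection. Section 4.1 already treats efficacy as strictly exploratory, which lowers the stakes but does not settle the rule. Both parts merit a change because the remedy is cheap.

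**What to change.** 1. **Ask once.** At Session 4, after GAMEX, add one yes/no item: during the study, did you see or use the other shift's screens, codes, missions or test questions? Put it on a separate anonymous slip marked by shift only, collected by the non-teaching co-author, and state that the answer has no consequence for grade or participation. Anonymity matters because the investigator enters the coded paper forms (section 2.9) and holds the identity key (section 2.11), so a coded item would still be an admission the teacher could read. Report the proportion by arm alongside the diary entries.
2. **Settle the analysis.** Reconcile section 2.3 with section 4.1: detected cross-contamination is no longer a reason to exclude data, these students are analysed in their allocated group, and a sensitivity analysis omits the diary-detected cases.

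The cost is one item beside 27 GAMEX items and one extra analysis. Because the slip is anonymous, its answers cannot be linked to individual learning gains, so the sensitivity analysis can use diary cases only. Asking at the end of Session 4 does little harm, since section 2.6 gives controls access to the experimental platform from then on.

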### 4.2. Dissemination Plan

The results of this pilot study will be disseminated through publication in high-impact, peer-reviewed journals in the fields of nursing education and medical informatics and presented at international conferences. Authorship eligibility will be determined according to the International Committee of Medical Journal Editors guidelines. A summary of the key findings, written in plain language, will be sent to all participants upon study completion.

Regardless of the statistical significance of the results, the de-identified individual participant data, the data dictionary, the statistical analysis code, and the specific AI prompts used to generate the narratives will be deposited in a public open-access repository upon publication. This ensures full transparency and allows for independent replication of the study findings.

## 5. Conclusions

This protocol presents a structured methodological framework to address the lack of personalization in simulation-based nursing education. The primary contribution of this study will be to establish the technical and pedagogical feasibility of using Generative AI to create profile-adapted clinical narratives, a process that has historically been resource-prohibitive for standard curricula.

Rather than assuming the superiority of the adapted method, this pilot study aims to provide the first empirical evidence regarding the relationship between player personality (PPDS profiles) and engagement with digital clinical cases. The data obtained will be critical to determining whether a “precision education” approach yields sufficient improvements in learning gains or satisfaction to warrant implementation in larger, randomized clinical trials.

Ultimately, the successful execution of this protocol will validate a scalable workflow for integrating psychometric profiling into the Learning Management Systems of health science faculties, potentially shifting the paradigm from “one-size-fits-all” simulations to student-centered adaptive training. By doing so, this research provides a novel and cost-effective blueprint to advance precision education in the nursing field.

## Figures and Tables

**Figure 1 nursrep-16-00104-f001:**
[figure not shown]
Schedule of enrollment, interventions, and assessments.

**Figure 2 nursrep-16-00104-f002:**

Schematic diagram of the daily 120 min session workflow.

**Table 1 nursrep-16-00104-t001:** Comparison of gamification elements between control and experimental groups.

Element	Control Group (Generic)	Experimental Group (Adapted to Profile)
Clinical Difficulty	Invariant. Identical clinical cases and complexity.	Invariant. Identical clinical cases and complexity.
Narrative Tone	Neutral, academic, and linear.	Adapted, e.g., “Epic/Heroic” for Tryhard; “Humorous/Satirical” for Joker; “Emotional/Empathetic” for Socializer.
Visual Esthetics	Standard medical imagery (clean, white/blue).	Adapted, e.g., “High-fantasy/Dark” for Esthetic; “Leaderboards/Badges” prominence for Tryhard.
Feedback Style	Correct/incorrect + standard explanation.	Adapted, e.g., “Challenge failed, try again!” (Tryhard) vs. “Don’t worry, let’s learn together” (Coacher).
Side Missions	None.	Specific: Hidden “Easter eggs” (Joker), esthetic puzzles (Esthetic), or speed challenges (Tryhard).

## Data Availability

The data relating to the implementation of the intervention and the results derived from this research will be available upon justified request to the corresponding authors.

## Abbreviations

The following abbreviations are used in this manuscript:

AI	Artificial Intelligence
CG	Control Group
EG	Experimental Group
GAMEX	Gamified Experience Scale
LG	Learning Gain
PI	Principal Investigator
